## Abstract

**Background:**

Irritable bowel syndrome (IBS) is a worldwide disease with high morbidity. The effect of current treatment with Western medicine is not satisfactory. Although moxibustion treatment is widely used for gastrointestinal diseases, randomized controlled trials on the use of this treatment for IBS are limited. This study aims to evaluate the clinical efficacy and safety of moxibustion treatment in patients with diarrhea-predominant irritable bowel syndrome (IBS-D).

**Methods/design:**

A multi-center, randomized, single-blind and placebo-controlled trial is employed. 104 cases will be divided into two groups: (1) a mild-warm moxibustion group in which moxa stick is 3–5 cm away from acupuncture points and the skin temperature is maintained at 43 ± 1 °C; and (2) a placebo moxibustion group in which moxa stick is 8–10 cm away from acupuncture points and the skin temperature is maintained at 37 ± 1 °C. Moxibustion is performed on bilateral ST25 and ST36 in the two groups for 30 min each time, three times a week for 6 weeks. The patients are followed up at the 12th and 18th weeks. Adequate relief is used as a primary outcome measure; IBS symptom severity score, Bristol stool form scale, IBS quality-of-life questionnaire, and hospital anxiety and depression scale are used as secondary outcome measures.

**Discussion:**

This study aims to demonstrate the safety and efficacy of moxibustion treatment for IBS-D, which may validate moxibustion as an effective therapy for treating IBS-D.

**Trial registration:**

ClinicalTrials.gov identifier NCT02421627 (8 April 2015).

## Background

Irritable bowel syndrome (IBS) is a chronic functional gastrointestinal disorder characterized by recurrent abdominal pain or discomfort in combination with disturbed bowel habits in the absence of an identifiable cause [1]. Currently, the morbidity of IBS is 7–21 % worldwide, it can occur at any age, mainly between 30 and 50 years [2, 3]. Of all types, diarrhea-predominant irritable bowel syndrome (IBS-D) is the most common subtype [4]. IBS has gained attention because it significantly reduces people’s quality of life (QOL) and influences medical resources and social economy [5, 6].

The pathogenesis of IBS is unclear. It is probably related to visceral hypersensitivity, brain–gut regulation dysfunction, intestinal infection and inflammation, and psychological factors [2, 7]. The current treatment for IBS is to remove the inducing factors and relieve the symptoms. However, the poor efficacy and the side effects from long-term drug use have forced patients to seek alternative interventions [8, 9]. In recent years, physicians as well as patients are more interested in complementary and alternative medicine including acupuncture and moxibustion [10, 11]. While much less popular than acupuncture, moxibustion exerts its effects through warm stimulation caused by burning moxa on the acupuncture points. Mild-warm moxibustion is a therapy in which a burning moxa stick is pointed to a moxibustion site (usually an acupuncture point) at a distance to make the patient have a warm sensation but without any burning pain. Because of its low cost and easy application, moxibustion is often used to treat gastrointestinal diseases. However, its efficacy on IBS has not been confirmed. Previous trials on the treatment of IBS with moxibustion were often lack of strict control of randomization and related risk of bias, which makes the conclusions less convincing [12]. A recent randomized controlled trial on herb-partitioned moxibustion for IBS also failed to fully confirm its effectiveness, and the results still need to be verified [13].

Therefore, a multi-center, parallel-group, 1:1 allocation, randomized, single-blind and placebo-controlled trial has been designed in this study. The aim is to evaluate the clinical efficacy and safety of moxibustion in patients with IBS-D. The results may provide evidence for the clinical use of moxibustion in patients with IBS-D.

## Methods/design

### Study design

This study is a multi-center, randomized, single-blind and placebo-controlled clinical trial. All the subjects will be enrolled according to the ROME III IBS-D diagnostic criteria [14]. The flowchart of the trial is shown in Fig. 1.

**Fig. 1 Fig1:**
[figure not shown]
Flow diagram of study design

### Patients

All the 104 cases will be recruited from the following three research centers: the Bowel Disease Clinic of the Shanghai Research Institute of Acupuncture and Meridian; the Department of Acupuncture-Moxibustion of the Yueyang Integrated Chinese and Western Medicine Hospital at the Shanghai University of Traditional Chinese Medicine (TCM); and the Department of Acupuncture-Moxibustion of the Shanghai TCM-Integrated Hospital, Shanghai University of TCM. Recruitment notices were released on TV, newspapers, and magazines. Also, recruiting posters were posted in the community and public places nearby to ensure enough subjects.

### Sample size calculation

Previous studies showed that the effective rates of the mild-warm moxibustion group and the placebo group were 88.7 % [15] and 62 % [16], respectively. Based on these values, the sample size in this study is estimated as follows:$$ n = {\left(Ua+Ub\right)}^2\left(1 + 1/k\right)P\left(1-P\right)/{\left(Pe-Pc\right)}^2 $$

The significant level is 0.05; the power of test is 1 − *β* = 0.9, *k* = 1; and the sample loss rate is 15 %. The required sample size is 52 by calculation, and no less than 104 cases should be included in the two groups.

### Randomization

In this study, random numbers are generated by SPSS and kept by a clinical research coordinator who has no contact with the patients. The allocation will be concealed in sequentially numbered, opaque, sealed envelopes containing the randomization assignments. An eligible subject who meets the inclusion criteria will sign the informed consent. Researchers in a research center will use a random number and grouping information sent by telephone, text message, or e-mail from the clinical research coordinator, and assign the subject into moxibustion or placebo moxibustion groups.

### Blinding

The practitioners could not be blinded due to the unique nature of moxibustion treatments. The patients are blinded to the treatment. They are kept in individual isolated rooms, avoiding communication among them. Furthermore, Researchers responsible for data collection, analysis, and statistics have no information about grouping and treatment.

### Eligibility

Inclusion criteria:Patients who are enrolled according to the ROME III IBS-D diagnostic criteriaPatients aged between 18 and 65 yearsPatients who have signed informed consent

Exclusion criteria:Patients who present with intestinal organic disordersPatients who have been administered drugs for treating IBS-D or other drugs that may influence the trialPatients who have a severe disease of the heart, brain, lung, liver, kidney, or hematopoietic systemPatients who are diagnosed with a psychiatric disorderWomen in pregnancy or nursingPatients who have a history of abdominal surgeryPatients who have been treated by acupuncture and moxibustion

### Interventions

#### Treatment group

For mild-warm moxibustion treatment, bilateral ST25 and ST36 points are used (reference for PRC National Standard GB/T 12346–2006) [17]. A moxa stick (diameter 3 cm) is ignited and positioned with a supporting device so that the tip of the moxa stick is 3–5 cm above the acupuncture point. The temperature of the acupuncture point is monitored with an infrared thermometer (Fluke 62, USA) and maintained at 43 ± 1 °C to make the subject feel warm without any burning pain. The treatment lasts for 30 min each time, three times a week for 6 weeks (18 times). After the treatment, follow-ups are made at weeks 12 and 18.

#### Control group

For the placebo moxibustion group, the same acupuncture points as the treatment group are used. The same type of moxa stick is ignited but kept 8–10 cm above the acupuncture point. The temperature of the acupuncture point is similarly monitored but maintained at 37 ± 1 °C so that the subjects do not to feel warm at the points. The treatment cycle and follow-up time are the same as the treatment group.

### Outcome measurements

#### Primary outcome

##### Adequate relief

Adequate relief (AR) is used to evaluate the degree of alleviation of IBS symptoms, with relief of abdominal pain or abdominal discomfort as the criterion. During the treatment and follow-up, the patients evaluate themselves once every week. The primary endpoint is set at the end of the treatment (week 6), and the statistics are also performed during follow-ups (weeks 12 and 18) for efficacy duration assessment. “Yes” is defined as positive symptom improvements in more than 3 weeks during the 6-week period; “no” is defined as positive symptom improvements in less than 3 weeks [18]. The indicator has been applied in several studies [19, 20] and was found to have significant correlations with intestinal function and QOL [21].

#### Secondary outcomes

##### IBS Symptom severity score

IBS symptom severity score (SSS) [22] is used to evaluate the degree of severity of IBS-D in the patients. A total score of 500 is calculated from abdominal pain degree, abdominal pain frequency, abdominal distension degree, defecation satisfaction, and influence on life. If the score is lower than 75, the patient is considered to be in remission. The mild, moderate, and severe boundary values are 75–175, 175–300, and above 300, respectively. The effectiveness, reliability, and sensitivity of IBS SSS to treatment are verified.

##### Bristol stool form scale

Grading standard in the Bristol stool form scale (BSS) [23] is employed to record stool characteristics of the patients with IBS-D in this study. The scale is a visual descriptive figure reflecting gastrointestinal transit time. The total score of the scale ranges from 1 to 7 according to the 1–7 types (from constipation to diarrhea) of stool characteristics.

##### Irritable bowel syndrome quality-of-life questionnaire

Irritable bowel syndrome quality-of-life questionnaire (IBS-QOL) is a specialized scale developed by Patrick et al. [24] for patients with IBS. It is composed of 34 items of self-assessment ranging from dysphoria, interference with activity, body image, health worry, food avoidance, social reaction, to sexual relationships, to assess QOL. The patients’ QOL is measured by a 5-point linear scale, and each question has a 5-point Likert scale (score 1–5). The total score of the scale ranges from 34 to 170. The scale achieves good measurement validity.

##### Hospital anxiety and depression scale

Hospital anxiety and depression scale (HADS) is used to assess the level of anxiety and depression in patients with IBS-D [25]. It comprises 14 questions, with seven questions each on anxiety and depression. Each question has a 4-point Likert scale (score 0–3). The total score of the scale ranges from 0 to 42. A score greater than 8 in each subscale indicates anxiety/depression.

IBS-SSS and BSS are completed before treatment (week 0), at the end of treatment (week 6), and during follow-ups (weeks 12 and 18). IBS-QOL and HADS are completed before treatment (week 0) and at the end of treatment (week 6). All the assessments are shown in Table 1.

**Table 1 Tab1:** Trial flowchart

Items		Before enrolment (weeks) –4 to 0	Intervention period (weeks) 1–6	End of 6-week treatment (weeks)	Follow-up (weeks) 7–12	End of 12-week follow-up (weeks)	Follow-up (weeks) 13–18	End of 18-week follow-up (weeks)
Recruitment		×						
Enrolment		×						
Inclusion criteria		×						
Exclusion criteria		×						
Informed consent		×						
Basic characteristic variables		×						
Randomization and allocation concealment		×						
Primary outcomes	AR		×	×	×	×	×	×
Secondary outcomes	SSS	×		×		×		×
	BSS	×		×		×		×
	IBS-QOL	×		×				
	HADS	×		×				
Safety outcome				×		×		×
Statistical analysis				×		×		×

### Safety outcome

In this study, possible adverse events during moxibustion include skin burns, blisters, pruritus, dizziness, and respiratory symptoms. The researchers record and deal with all the adverse events (no matter whether it is relevant with moxibustion). When necessary, the researchers can decide whether the trial is terminated.

### Quality control

All the researchers are practicing doctors certified by the Ministry of Health of the People’s Republic of China. They must have more than 5 years of clinical experience and be qualified as attending physicians. All the researchers are trained to improve consistency among subjects. The outcomes are assessed for all the subjects. The outcome measurement data are preserved in the original case report form (CRF), and supervised and checked by a qualified clinical research coordinator. The original data are recorded into the electronic medical records using a double data entry method by trained researchers, and the electronic data are consistent with the original data. To improve compliance of the subjects, each subject who completes the trial is provided a cash reward.

### Data monitoring

This study has set up an independent clinical trial data monitoring committee (DMC), which comprises a medical expert and two clinical research experts. The DMC verifies whether the trial follows the study design and the standard guidelines, checks research progress and the accuracy and authenticity of the CRF, and checks whether the reasons for discontinuation of subjects and adverse events have been recorded in detail in the CRF. In the case of any serious adverse events, the DMC discusses with the institutional review board and the principal investigator, and the principal investigator makes a final decision on the continuation or termination of the trial. In addition, the institutional review board also makes recommendation to the principal investigator on stopping the trial if a serious adverse event occurs.

### Statistical analysis

The statisticians are responsible for coordinating research efforts, making a statistical analysis plan, and building a research database. Both intention-to-treat and per-protocol analyses are performed. The last-observation-carried-forward method is used for missing data in the intention-to-treat analysis. SPSS16.0 software is used to analyze the data. Measurement data are first tested using the normality test. Data conforming to the normal distributions are expressed as mean ± standard deviation, while data not conforming to the normal distributions are expressed as M (P25–P75). A paired *t* test or nonparametric test is used to perform intragroup comparison, and a two-sample *t* test or nonparametric test is used to perform comparison among groups. Enumeration data is expressed as a case (ratio) and analyzed using the *χ*
^2^ test. Statistic significance is defined as *p* < 0.05.

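### LOCF is the only missing-data rule for the intention-to-treat analysis, so with 15% loss expected the results for dropouts rest on an arbitrary last value, with bias of unknown size and direction

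*Protocol article*

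**What the plan says.** The Statistical analysis section of the protocol article names two analysis sets: "Both intention-to-treat and per-protocol analyses are performed". It then fixes one rule for incomplete data: "The last-observation-carried-forward method is used for missing data in the intention-to-treat analysis". It excepts no outcome and names no alternative missing-data analysis. Under Sample size calculation the plan assumes that "the sample loss rate is 15" per cent, with 52 patients per group.

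For the primary outcome, the Adequate relief section says that "the patients evaluate themselves once every week" during treatment and follow-up. A yes "is defined as positive symptom improvements in more than 3 weeks during the 6-week period", a no is fewer than 3 such weeks, and exactly 3 is not assigned. The primary endpoint is at week 6, and "the statistics are also performed during follow-ups (weeks 12 and 18) for efficacy duration assessment".

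The schedule at the end of Secondary outcomes, and Table 1, place IBS-QOL and HADS at weeks 0 and 6 only, and IBS-SSS and BSS at weeks 0, 6, 12 and 18.

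**The concern.** LOCF assumes that a patient who leaves stays as last seen. Here that assumption meets three features of the design.

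- The primary endpoint is a count of weekly answers, so one answer may be copied several times and then counted.
- Weeks 12 and 18 exist to show whether the effect lasts. A carried value assumes that it lasts, or that it is still absent.
- All four secondary scales have only the baseline value before week 6, so carrying forward means imputing no change.

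About one patient in seven is expected to be lost, so the treatment comparison could depend on the imputation rule as well as on the treatment. The per-protocol analysis is no check on this. It selects patients by adherence and does not vary the assumption about missing values.

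**Working it through.** **Inputs.** From the protocol article: 52 per arm, 15% loss, and assumed response of 88.7% and 62% (Sample size calculation); more than 3 positive weeks of 6 for a yes (Adequate relief); the visit schedule (Table 1). Expected loss is 0.15 × 52 = 7.8, about 8 per arm. The 52 does not depend on LOCF. The plan's formula with a one-sided 0.05 level gives 44.6, and 44.6/0.85 = 52.5 or 44.6 × 1.15 = 51.3. Sidedness is a separate matter.

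**1. Primary endpoint, LOCF on weekly answers.** Take a patient last seen in week *w* whose only positive answer is the last. The count after imputation is 1 + (6 − *w*).

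| Last week seen | Positive weeks after LOCF | Status |
|---|---|---|
| 1 | 6 | yes |
| 2 | 5 | yes |
| 3 | 4 | yes |
| 4 | 3 | not assigned |
| 5 | 2 | no |
| 6 | 1 | no |

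Listing every answer pattern for a last visit in weeks 1 to 3 shows that the last answer alone decides. Half of the patterns become responders (1 of 2, 2 of 4, 4 of 8) and half non-responders. In week 3, for example, no-no-yes gives 4, and yes-yes-no gives 2.

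**2. Primary endpoint, LOCF on the 6-week status.** A patient who leaves before week 6 has no earlier status and AR has no baseline rating, so the rule yields no value. The article does not say which reading applies.

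**3. Effect on the AR comparison (illustration).** Assume 62% true response in both arms, 15% lost from each arm by week 3, and a last answer of yes in a fraction *f* of dropouts. The analysed rate is 0.85 × 0.62 + 0.15 × *f*, so the spurious difference is 0.15 × (*f*₁ − *f*₂). Rejection is by exact enumeration of the two-sided 5% chi-square test with 52 per arm.

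| Last answer yes, arm 1 / arm 2 | Analysed rates | Spurious difference | Rejection rate |
|---|---|---|---|
| no loss | 62% / 62% | 0 | 5.5% |
| any equal split | equal | 0 | about 5–6% |
| 70% / 50% | 63.2% / 60.2% | 3 points | 6.7% |
| 80% / 40% | 64.7% / 58.7% | 6 points | 10.4% |
| 80% / 20% | 64.7% / 55.7% | 9 points | 16.9% |
| 100% / 0% | 67.7% / 52.7% | 15 points | 36.8% |

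Arm 1 may be either arm. The table is the same in the opposite direction.

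**4. Duration (illustration).** Let 15% of week-6 responders be lost afterwards and carried as responders. Let a fraction *r* of responders truly keep their relief, and let no non-responder gain it. The true rate is p*r*, and the LOCF rate is p(0.85*r* + 0.15).

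| *r* | Moxibustion, true / LOCF | Placebo, true / LOCF | Difference, true / LOCF |
|---|---|---|---|
| 60% | 53.2% / 58.5% | 37.2% / 40.9% | 16.0 / 17.6 points |
| 40% | 35.5% / 43.5% | 24.8% / 30.4% | 10.7 / 13.1 points |

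This is exact for carried status. With carried weekly answers it holds for those whose last answer was yes.

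**5. Scales at week 6.** For IBS-QOL, HADS, IBS-SSS and BSS the only earlier value is week 0, so each missing value is set to zero change. With 15% missing in both arms, the difference in mean change is 0.85 times its value among completers.

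**The case against.** The strongest reply is that the effect on AR is conditional throughout. The article does not say that LOCF acts on weekly answers, and under the other reading step 1 disappears. The dropout splits in step 3 are assumptions, and mild imbalance does little (6.7% at 70/50). Patient blinding, isolated rooms and a cash reward for completion all work against unequal loss. The zero-change imputation is usually conservative. Modelling choices are also commonly left to the SAP.

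Much of this stands, and it rules out a stronger reading. A reader might infer that any early dropout with one good week is turned into a responder, or that the rule favours moxibustion. The documents support neither. One good week suffices only under weekly carrying, when it is the last week seen and falls in weeks 1 to 3. A last answer of no pushes the other way, and nothing in the article indicates how last answers would differ by arm.

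The reply does not rescue the rule. The article has made the choice itself, so an SAP that follows it inherits the problem. The alternative reading leaves early dropouts without a primary outcome, which is also a defect. The design features lessen unequal loss but cannot exclude it: Safety outcome lists burns and blisters, and the Discussion accepts that patients may become aware of their treatment.

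A fair objection also applies to the obvious replacement. Counting missing weeks as not relieved is itself a single imputation. With 62% true response in both arms and early loss of 10% and 20%, it gives 55.8% against 49.6% and an 11.4% rejection rate.

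**Conclusion.** The point holds: LOCF is a stated rule that gives a poor result here and can be replaced cheaply.

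Two parts follow from the schedule alone. A missing week-6 value of any of the four scales becomes the baseline value, shrinking the difference to about 85% under equal 15% loss. AR dropouts before week 4 are either classified by one answer or left without a value.

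The size and direction of bias in the AR comparison are not determined by the documents. Under the stated assumptions the false-positive rate runs from the usual 5–6% with equal splits to 17% at 80/20 and 37% in the extreme case, for or against moxibustion.

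It would go too far to say that the rule creates durability in general. It overstates retention for responders lost after week 6 who later relapse, while carried non-responders stay non-responders. The between-arm excess in the illustration (1.6 and 2.4 points) requires a difference at week 6 to begin with.

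**What to change.** Replace LOCF while recruitment is still open, and state the rule for each outcome.

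- **AR.** Choose one as primary and keep the other as a sensitivity analysis: multiple imputation of the weekly answers, or counting a missing week as not relieved, so that a yes needs at least 4 recorded positive weeks in each 6-week period. Add a tipping-point analysis that varies the response of dropouts separately by arm.
- **IBS-SSS and BSS.** Use a mixed model for repeated measures with baseline, arm, visit and arm-by-visit terms.
- **IBS-QOL and HADS.** Use a baseline-adjusted comparison with multiple imputation.

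The cost is plan wording and modest analysis work, with no new visits or data. If missing counts as not relieved, responder rates fall in both arms. At the plan's rates with all 15% lost early, they are 0.85 × 88.7% = 75.4% and 0.85 × 62% = 52.7%, with about 69% two-sided power at 52 per arm, against about 90% without loss. That rule is also biased when loss differs by arm, so the sensitivity analyses are a necessary part of the change.

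### The four secondary scales are compared between arms without baseline adjustment although each is measured at week 0, which gives up precision whether post-treatment or change scores are compared

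*Protocol article*

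**What the plan says.** The abstract lists the scales: "IBS symptom severity score, Bristol stool form scale, IBS quality-of-life questionnaire, and hospital anxiety and depression scale are used as secondary outcome measures". The assessment schedule, under the heading for the hospital anxiety and depression scale, gives their timing: "IBS-SSS and BSS are completed before treatment (week 0), at the end of treatment (week 6), and during follow-ups (weeks 12 and 18"), and "IBS-QOL and HADS are completed before treatment (week 0) and at the end of treatment (week 6"). Table 1 agrees. Every scale therefore has a pre-treatment value.

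The Statistical analysis section sets out three steps for continuous data:

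- "Measurement data are first tested using the normality test". The result decides how the data are summarised.
- Within each arm, a paired t "test or nonparametric test is used to perform intragroup comparison".
- Between arms, a two-sample t "test or nonparametric test is used to perform comparison among groups".

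One threshold, p < 0.05, covers all of these tests. No covariate, ANCOVA or repeated-measures model is named. The section does not say whether the between-arm test is run on post-treatment scores or on changes from week 0, or how the within-arm results will be read. It mentions that the statisticians make an analysis plan, which is not shown.

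**The concern.** The article names the tests, so this is a stated method that can be judged as it stands. Three features of it matter.

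1. **No baseline adjustment.** The week-0 score of the same scale is usually one of the best predictors of the later score. Leaving it out of the between-arm comparison widens the confidence interval. If post-treatment scores are compared, it also leaves any chance baseline imbalance in the estimate.
2. **Method left to the data.** If the normality test also picks the comparison, one scale could be compared by means at week 6 and by ranks at week 12. The quantity estimated would then not be fixed beforehand.
3. **Within-arm tests beside between-arm tests.** A paired test in one arm cannot separate a treatment effect from placebo response, which the Discussion gives as the reason for having the placebo arm. Nothing labels these tests as descriptive.

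**Working it through.** **Inputs from the article:** 52 patients per arm with 1:1 allocation; loss stated as "and the sample loss rate is 15" %, so 52 × 0.85 ≈ 44; significance level 0.05, sidedness not stated.

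**Assumed, because the article gives no SD, correlation or effect size for any scale:** baseline-to-outcome correlation r = 0.3, 0.5, 0.7; equal SD at both times and in both arms; a true effect of 0.5 SD for the power figures; two-sided 0.05.

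**The plan's own figure.** The only stated sample size is 52 per arm, for the binary primary outcome. With P = (0.887 + 0.62)/2 = 0.7535, the article's formula at one-sided 0.05 and 90 % power gives 44.6, so 45, and 45 × 1.15 = 51.75, so 52. It serves here only as the number per arm. There is no figure for the scales to reproduce.

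**Step 1: variance.** With outcome variance 1, the variance per patient is 1 for a post score, 2(1 − r) for a change score and 1 − r² for ANCOVA. Hence ANCOVA/post = 1 − r², and ANCOVA/change = (1 − r²)/(2(1 − r)) = (1 + r)/2.

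| r | ANCOVA/post | Extra patients the post-score test needs | ANCOVA/change | Extra patients the change-score test needs |
|---|---|---|---|---|
| 0.3 | 0.91 | 1/0.91 − 1 = 10 % | 0.65 | 1/0.65 − 1 = 54 % |
| 0.5 | 0.75 | 1/0.75 − 1 = 33 % | 0.75 | 1/0.75 − 1 = 33 % |
| 0.7 | 0.51 | 1/0.51 − 1 = 96 % | 0.85 | 1/0.85 − 1 = 18 % |

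Both ratios are below 1 for every r between 0 and 1 (exclusive), so the gain does not depend on which score the authors meant. The small cost of estimating the slope is ignored. For a rank test the ratios are only a guide.

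**Step 2: power for 0.5 SD** (normal approximation with residual SD 1, √(2(1 − r)) or √(1 − r²)).

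| Per arm | Post score | Change score, r = 0.3 / 0.5 / 0.7 | ANCOVA, r = 0.3 / 0.5 / 0.7 |
|---|---|---|---|
| 52 | 72 % | 58 / 72 / 91 % | 76 / 84 / 95 % |
| 44 | 65 % | 51 / 65 / 86 % | 69 / 77 / 91 % |

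At 52 per arm the gain is about 4 to 22 points over post scores and about 4 to 19 points over change scores.

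**Step 3: chance imbalance, post scores only.** The SE of the baseline difference is √(2/52) = 0.196 SD. An imbalance of 0.39 SD (about 2 SE) shifts the null comparison by r × 0.39 = 0.117, 0.195 or 0.273 SD. Conditional type I error becomes 8, 13 or 21 % for r = 0.3, 0.5 or 0.7. At an imbalance of 0.2 SD it is 5.0, 4.9 or 4.1 %, so only a large imbalance does harm. Averaged over all randomizations the error stays at 5 %.

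**Step 4: within-arm tests with no treatment effect.** Let both arms improve equally, with r = 0.5 and 52 per arm. If p is the chance that one arm's paired test is significant, exactly one arm is significant with probability 2p(1 − p).

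| Improvement in each arm | p | Exactly one arm | Active arm only |
|---|---|---|---|
| 0.2 SD | 0.293 | 0.415 | 0.207 |
| 0.3 SD | 0.565 | 0.492 | 0.246 |
| 0.4 SD | 0.808 | 0.311 | 0.155 |
| 0.5 SD | 0.943 | 0.108 | 0.054 |

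At 0.5 SD both arms are significant in 0.943² = 89 % of trials. With no treatment effect at all, one arm or both may reach significance.

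**Step 5: normality pre-test as selector.** In 10,000 simulated null trials of 52 per arm, choosing the t test or the rank test by a normality test gave a type I error of 0.052 with normal data and 0.049 with skewed (gamma) data.

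**The case against.** The strongest defence is that nothing planned here is invalid. Two-sample tests hold their level under randomization, the scales are secondary, no power is claimed for them, and the binary primary outcome is untouched. The article is also condensed, and covariates are often settled in an analysis plan. The first part stands and limits the weight of the point. The second does not remove it, because the article commits to particular tests rather than leaving the method open.

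The size of the gain also rests on an assumed r. That stands too: against post scores the saving in patients runs from 10 to 96 %, so no single value should be quoted as the gain. Linear ANCOVA is open to debate for the 1–7 BSS, and the fix allows for that.

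A reader might infer more than the text supports:

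- **That baseline is ignored.** This would be true of the between-arm test only if post scores are compared. The article leaves that open, a change-score comparison would use baseline, and the paired tests do use it. What is certain is that no adjustment is planned.
- **That the 62 % placebo rate in the sample size section makes the paired tests significant in both arms.** That is a binary response rate from an earlier study. It gives no mean change or SD on these scales.
- **That the authors intend before-after claims of efficacy.** Between-arm tests are planned as well, and no passage treats a within-arm p-value as evidence of efficacy.
- **That the normality test inflates false positives.** Its role as test selector is only implied, since the text ties it explicitly to summary statistics, and the simulation showed no inflation.
- **That about 44 per arm will be analysed.** The intention-to-treat analysis carries the last observation forward, so it can keep up to 52. A figure near 44 fits the per-protocol analysis at the assumed loss.

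**Conclusion.** The point holds as one of efficiency and prior specification on secondary outcomes. The between-arm comparison of four scales with a week-0 value uses no baseline adjustment, and precision is lost whichever score is compared: variance ratios 0.91/0.75/0.51 against post scores and 0.65/0.75/0.85 against change scores for r = 0.3/0.5/0.7. These figures rest on the assumed r and on equal SDs; the power figures also assume a 0.5 SD effect. The harm from the normality step is a comparison left to the data. The harm from the paired tests is a risk of misreading. The documents do not support calling the planned tests biased or invalid. The change is worth making because the data for it are already scheduled.

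**What to change.** Change the analysis wording as follows:

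- **IBS-SSS, IBS-QOL, HADS:** make the main between-arm analysis an ANCOVA with the week-0 score and centre as covariates. For IBS-SSS, which also has weeks 6, 12 and 18, a repeated-measures model with the same covariates may be used instead. Report the adjusted mean difference with its 95 % CI.
- **BSS:** use a baseline-adjusted ordinal or rank-based analysis, or ANCOVA with a rank-based sensitivity analysis.
- **Choice of method:** fix it in advance and do not let a normality test decide. Keep a rank-based or bootstrap analysis as sensitivity.
- **Within-arm paired tests:** report them as descriptive only and state that they are not evidence of efficacy.

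The cost is wording. Week-0 scores are already scheduled for every scale and the three centres are known, so no new data, visits or patients are needed. The Trial status section describes the trial as still recruiting, so on that account the change can be settled before the data are analysed.
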